### Data monitoring

A central project data manager will perform data quality control on all collected data. A flow chart will be created to describe the number of consecutively recruited patients who had a rotator cuff repair by arthroscopic procedure or had a conversion to an open procedure, and who completed follow-up clinical and imaging examinations as well as self-reported outcome questionnaires. The reasons for patient dropout and loss to follow-up status will be monitored and described. All recorded study parameters will be described using standard descriptive statistics; continuous variables will be presented as means with SD and categorical variables as counts with percentages. The variability of data between clinics will be explored to support the identification of outlier data.

Weekly site-specific reports, including the patient enrolment list, expected follow-up timing and identification of missing, erroneous or inconsistent data, are sent to the respective local project staff. Data-related queries will be resolved remotely or by on-site monitoring visits before the final analyses are performed.

There is no plan for auditing project conduct other than via reporting at the annual meetings of the project scientific board (PSB).

### Data management

Study data will be stored using the REDCap web-based electronic data capture system^70 71^ on a server that is hosted at Schulthess Klinik. REDCap conforms with Good Clinical Practice guidelines, which provide the required features for data protection and integrity, for example, password-protected access and change tracking.

Study data will be coded and exported from the REDCap system into the Stata software version 16 for statistical analyses. Data transformations and analyses will be primarily implemented using Stata and fully documented within Stata programming files. Data subsets will be prepared for analyses using alternative software (eg, R for prediction models) as appropriate.

All patients with an intraoperatively confirmed rotator cuff tear and operated by ARCR will be included in the analyses. Existing missing data will be imputed if the number of missing data is non-negligible or could potentially bias the results and conclusions.

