### Eligibility criteria

Adult patients diagnosed with a partial or full-thickness rotator cuff tear by MRI, planned for a primary arthroscopic surgical repair and giving their informed consent to participate in the cohort study will be included. Patients undergoing a specific surgical procedure for irreparable tears (ie, tendon transfer, subacromial spacer or superior capsular reconstruction), revision operations, and open or mini-open reconstructions will be excluded. Patients unable to provide written informed consent or attend clinics for follow-up visits, not fluent in German, French, Italian or English, or pregnant women will be excluded.

Patients undergoing bilateral ARCR will only be included for their first intervention.

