### AE documentation and assessment process

The operating surgeons will report the occurrence of any intraoperative AE on the operation form. The occurrence of postoperative local AEs within 24 months will be reported by investigators at the clinical examination and by patients on the questionnaires. The occurrence of postoperative non-local AEs that are unrelated to the operation will be documented in a similar manner, however only within 6 months after surgery. An AE form was developed according to the ARCR CES 1.0.^23^ Each AE documentation will be structured after Audigé *et al*^63^ and includes the date/period of occurrence (intraoperative/postoperative), the affected body location (local at the operated shoulder/non-local), the event group and specification, applied health-related intervention(s) (operative/non-operative procedure(s)), its outcome at the time of reporting (or end of the study), and the assessment of the event (causal factor(s)/severity grade/seriousness). Severity grading will be made according to existing and adapted systems for intraoperative^64 65^ and postoperative^12 36^ complications.

The documentation of AEs will be checked for completeness and consistency remotely as well as on-site by reviewing selected patient files as part of the monitoring plan. A review committee ([name]) will assess all events reported by surgeons and patients and generate queries to the respective sites as required.

Fully documented local events, including their treatment, outcome and possible causative factors, will be formulated in layman’s terms and sent back to the affected patients so that they can confirm and validate collected AE data as well as assess their severity on a Visual Analogue Scale from 0 (not at all severe) to 100 (extremely severe). This subsequent rating will also be performed by their treating surgeon and four other randomly selected surgeons involved in the project, blinded to the original severity grading.

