### Recruitment

Study sites and local investigators were selected based on their expertise in ARCR, with support from the shoulder and elbow expert group of Swiss Orthopaedics. Each site was visited by the project leaders to assess the adequacy of local clinical and research settings for the project as well as to ensure prior interest and commitment. The number of included sites was determined based on the reported estimate of the number of ARCR patients that could be realistically enrolled within 1 year from each site and included an allowance for overestimation (ie, all sites together estimated that they could recruit up to 40% more than the expected 970 patients within 1 year).

Patients who are enrolled after signing an informed consent form are definitively recruited for the project after documentation of baseline parameters (clinical examinations and patient questionnaires) and confirmation of ARCR during surgery. A recruitment curve is prepared every 2 weeks and sent to the project sites along with a recruitment table presenting the performance of each site. Sites that are unable to recruit the expected number of patients within the first 3 months will be considered for exclusion from the project and replaced by additional sites if the estimated total duration of patient enrolment is delayed for more than 3 months.

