### Scientific relevance and broader impact

This project initiates the development of personalised risk predictions to support the surgical decision process in ARCR. The consensus CES may become an international reference for the reporting of complications in clinical studies and registries, and may therefore provide a solid metric for the documentation of surgical safety in ARCR. Methodological insight gained from this project will be easily transferable to similar initiatives and thus may foster the realisation of other cohorts on safety and effectiveness outcome in shoulder surgery (eg, arthroplasty) and orthopaedics in general.

For patients affected by rotator cuff tears and their surgeons, this study will be the first to provide solid data on the incidence of patient-validated AEs and other core outcomes up to 2 years after surgical repair based on international consensus COS and CES. This study will allow the investigation of a comprehensive list of potential prognostic factors to generate predictive models for these core outcomes and hence offer personalised health information to support future patients and surgeons in the decision process for surgery. Outcome predictors and risk calculators are increasingly being developed in numerous medical fields including surgery and orthopaedics, and they are in development in the field of ARCR.

This study will assess the structure and content of the ARCR CES and consolidate its validity in capturing unfavourable events of importance to both patients and surgeons; considering the patient’s perspective is an essential step in the development of a COS. Furthermore, the validation of an adapted severity classification of AEs in this study will provide an essential system for assessing surgical morbidity in orthopaedics. We expect that the ARCR CES and the event severity classification will become international standards for the reporting of ARCR AEs in clinical studies and registries, and therefore provide a solid metric for the documentation of surgical safety in ARCR.

This study fosters the enterprise in developing a Swiss-wide registry of ARCR, which will allow the ongoing evaluation and prediction of targeted core safety and clinical and patient-reported outcomes. The identification of factors mostly associated with relevant outcomes will facilitate a lean and straightforward documentation process for ARCR patients in Switzerland and abroad.

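### Patients whose planned arthroscopic repair is changed during surgery fall outside the analysis set, so an intraoperative adverse event that forces conversion is not counted in the adverse event incidence

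*Protocol article*

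**What the plan says.** Four sections of the protocol article bear on who is counted.

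- **Eligibility criteria.** Inclusion is decided before surgery: patients "planned for a primary arthroscopic surgical repair and giving their informed consent to participate in the cohort study will be included". The same section states that "revision operations, and open or mini-open reconstructions will be excluded", and it also excludes tendon transfer, subacromial spacer and superior capsular reconstruction for irreparable tears.
- **Recruitment.** Patients who have signed consent are "definitively recruited for the project after documentation of baseline parameters (clinical examinations and patient questionnaires) and confirmation of ARCR during surgery".
- **Data monitoring.** The planned flow chart covers consecutively recruited patients and has a category for conversion to an open procedure.
- **Data management.** "All patients with an intraoperatively confirmed rotator cuff tear and operated by ARCR will be included in the analyses". No separate population for safety is named.

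On adverse events, the section on AE documentation says: "The operating surgeons will report the occurrence of any intraoperative AE on the operation form". The Outcomes section lists all AEs reported by clinicians and patients as a safety outcome. The Adverse events section defines incidence as patients with an event over patients observed, with a Wilson interval. On intended use, the article says the models should "offer personalised health information to support future patients and surgeons in the decision process for surgery".

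**The concern.** Membership of the analysis set is decided by the course of the operation, after consent and baseline. The Intervention section describes a diagnostic arthroscopy followed by tendon mobilisation, so the final procedure can still change in theatre.

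For intraoperative safety this matters because an AE that makes the surgeon convert is both an event to be counted and the reason the patient is no longer counted. That loss is not random with respect to the outcome.

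There is also a point of interpretation for the models. They are meant to inform the decision for surgery, when nobody knows whether the repair will be completed arthroscopically. The article does not say that the predictions are conditional on completion.

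**Working it through.** **1. The sections side by side.** Take a consented patient with complete baseline data who is converted to open repair after an intraoperative AE.

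- Eligibility criteria: included at planning, then met by the exclusion of open reconstructions.
- Recruitment: not definitively recruited, because ARCR was not confirmed.
- Data monitoring: shown in the flow chart as a recruited patient with conversion. This conflicts with the Recruitment section.
- AE documentation: the event belongs on the operation form. The text does not say whether the form is completed for a patient who is not definitively recruited.
- Data management: outside the analyses.
- Adverse events: counted only if this patient is among those observed, which the text does not settle.

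Read literally, the event may be recorded but does not enter the incidence.

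**2. The plan's own number, to fix the base.** Sample size determination gives 920 patients plus 50 for 5% dropout. Check: 920 / (1 − 0.05) = 968.4, so 969, against 970 stated. This agrees. Under the Recruitment section the 970 are counted after ARCR is confirmed, so patients left out are additional to the 970 and the rule costs no sample size. Only if the 970 were counted at consent would precision suffer: with an assumed 1% or 5% left out, 970 × 0.99 × 0.95 = 912 or 970 × 0.95 × 0.95 = 875 would remain after dropout, below 920.

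**3. Effect on intraoperative AE incidence.** The article gives no rates, so all inputs here are assumptions. Let c be the share of operated patients left out, r the intraoperative AE rate in completed ARCR, and q the rate in those left out. The plan reports r. The incidence over all started procedures is

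(1 − c) × r + c × q.

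Example: c = 1%, r = 1%, q = 20% gives 0.99 × 0.01 + 0.01 × 0.20 = 1.2%. The number operated is 970 / (1 − c).

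| c | Operated | Left out | All-started incidence if r = 1% (q = 20% to 100%) | If r = 3% (q = 20% to 100%) |
|---|---|---|---|---|
| 0.5% | 975 | 5 | 1.1% to 1.5% | 3.1% to 3.5% |
| 1% | 980 | 10 | 1.2% to 2.0% | 3.2% to 4.0% |
| 2% | 990 | 20 | 1.4% to 3.0% | 3.3% to 4.9% |
| 5% | 1021 | 51 | 2.0% to 6.0% | 3.9% to 7.9% |

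The upper ends assume that every patient left out had an AE, which is an extreme.

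**4. Direction.** Leaving out a patient who had an event always lowers the proportion. Leaving out event-free patients raises it slightly: with c = 5%, r = 3% and q = 0, the all-started figure is 0.95 × 3% = 2.85% against 3% reported. The net effect is an understatement whenever q exceeds r.

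**5. Sensitivity to the AE-driven part.** Suppose 2% of started procedures have an AE without conversion, and a share x is converted because of an AE. The plan reports 0.02 / (1 − x), against 0.02 + x.

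- x = 1%: 2.02% against 3.0%, about one third too low.
- x = 0.1%: 2.00% against 2.1%, about 5% too low.

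**The case against.** The strongest reply is that completed ARCR is the declared target population. The objectives and the design section describe a cohort of patients undergoing ARCR, and both primary outcomes (six-month OSS change and postoperative stiffness) presuppose that the repair took place. That stands, and the population for the models should not change. The models also use operative and postoperative variables as predictors, so they visibly assume that surgery was done. A wider population would not by itself make them preoperative tools.

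It can also be said that nothing is hidden: surgeons report any intraoperative AE, the flow chart shows conversions, and the AE incidence has its own denominator. This stands in part. A reader might infer that these events go unrecorded. The article does not say so; what it does is restrict the analyses. But a conversion count in a flow chart does not put the associated AE into the incidence, and a denominator of patients observed does not clearly override the general analysis rule.

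A reader might further infer that all irreparable or severe tears drop out, which would make the models optimistic. The text does not support that. It excludes open surgery and three named procedures. A severe tear that is still repaired arthroscopically stays in, and a tear found irreparable but handled arthroscopically in some other way is not clearly removed.

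Finally, the AE objective concentrates on events up to 24 months after surgery. Intraoperative events are a small part of it, and no primary outcome depends on them.

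**Conclusion.** The point holds as a minor one, on a secondary safety outcome. The sections on eligibility, recruitment, data monitoring and data management do not agree on whether a converted patient belongs to the cohort. Followed literally, the analysis rule drops an intraoperative AE that caused a conversion, although the plan sets out to count all such AEs.

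Each event lost this way lowers the reported intraoperative rate. How much cannot be known from the article and may be very little. The figures above show only that the result depends entirely on assumed rates: the same calculation gives an understatement of about 5% or about one third, depending on one assumption. It would be wrong to quote either as the size of the bias. It would also be wrong to infer a loss from the planned 970, since recruitment is counted after ARCR is confirmed.

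For the OSS and stiffness models there is no error in the population, only a condition that should be stated.

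**What to change.** 1. Reconcile Eligibility criteria, Recruitment, Data monitoring and Data management, so that it is clear whether a patient whose procedure changes in theatre is a recruited patient.
2. For intraoperative AE incidence only (Outcomes and Adverse events), define the denominator as all consented patients in whom arthroscopy for a planned primary ARCR was started. Tabulate conversions and changes of procedure with their reason and any AE.
3. Keep completed ARCR as the population for the OSS and stiffness models and for postoperative AEs. State that the predictions are conditional on a completed arthroscopic repair, and report the proportion not completed beside them.

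The cost is a change of wording and completion of the operation form for converted or changed cases, in patients who have already consented. No extra visits or larger sample are needed. The intraoperative AE rate may come out slightly less favourable.

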### Systematic review of prognostic factors

A systematic review of prognostic factors for ARCR outcomes is implemented (PROSPERO registration number: CRD42020199257). Briefly, literature from 2014 to 2020 will be checked to identify longitudinal studies including patients diagnosed with a rotator cuff tear. These studies should report the effect of at least one factor on one of the following outcomes: shoulder stiffness, rotator cuff tear repair integrity and shoulder function. Data extraction will follow a predefined template and the collected data will be stored within a separate database using REDCap. Data from different studies will be described and may be synthesised depending on the data type and heterogeneity. These data will be used to generate a list of factors most likely to influence our project outcomes and therefore should be considered for inclusion in the predictive model development process.

### Predictive model development

To develop the predictive model(s), the seven steps proposed by Steyerberg *et al*^72 73^ will be used. The steps comprise (1) consideration of the research question and initial data inspection; (2) coding of the predictors; (3) model specification; (4) model estimation; (5) evaluation of model performance; (6) internal validation; and (7) model presentation.

Depending on the type of outcome, different models will be fitted and evaluated, that is, multiple regression models for the change in OSS at 6 months and multivariable logistic regression models for shoulder stiffness. Model diagnostics will be performed for all models to check the underlying assumptions.

The prediction of the model(s) will be based on the baseline, operative and postoperative management variables. First, a subset of the potential prognostic factors will be defined based on whether it is thought to be most predictive. The subset will be selected separately for each outcome by the Delphi method among the investigators, whereby the factors will be noted for their known or potential prognostic value on a 5-point Likert scale from 1 (not important) to 5 (extremely important). The factors with the highest mean score among investigators will form the subset.

We will then use criterion-based procedures (eg, Akaike information criterion or adjusted R^2^) to select the best set of predictors for the continuous outcome(s), and for the binary outcome we will use the area under the receiving operating characteristics curve.

To assess the predictive performance of the final models as well as the updated version of the prediction models, calibration plot and discrimination measures will be used. Thereby, apparent performance will be evaluated on the respective development data, and internal validated performance will be determined by bootstrapping. Independent external validation will be estimated by applying the resulting models from the development data set in the respective validation data sets. The resulting models will be used to predict the change of outcome value (ie, OSS in 6 months) and assess whether a patient will experience the event (ie, shoulder stiffness).

If we observe missing data, then missing data imputation will be performed using a method that allows for uncertainty in the imputed values (eg, multiple imputations using chained equation^74^). We will account for the clustering of records within clinics as appropriate.

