**Ethics and dissemination:**

This project contributes to the development of personalised risk predictions for supporting the surgical decision process in ARCR. The consensus CES may become an international reference for the reporting of complications in clinical studies and registries. Ethical approval was obtained on 1 April 2020 from the lead ethics committee (EKNZ, Basel, Switzerland; ID: 2019-02076). All participants will provide informed written consent before enrolment in the study.

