Appropriate indication of ARCR and judgement on risks of AEs or unsatisfactory patient outcomes rely on validated clinical prediction tools,^24 25^ which are still sparse in the field of surgical repair of a rotator cuff tear. Currently existing models focus on early surgical repair,^26^ tendon healing^27 28^ or shoulder functional outcomes.^29^ A model for shoulder stiffness included patients with various shoulder pathologies and surgeries.^30^ Furthermore, individual outcome predictions in ARCR require the identification of relevant patient and management factors. Several systematic reviews have highlighted the general lack of qualitative studies focused on prognostic factors for ARCR outcomes.^31–35^ In addition, we have observed substantial heterogeneity in terms of applied methodology, core outcomes and studied prognostic factors, where certain factors (eg, age, tear size, muscle degeneration, smoking) are given greater focus over others (eg, sex, traumatic onset). The reviews highlight the need for more robust prospective studies to include additional patient-reported outcomes in a multivariable context.

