### Outcomes

The *first primary outcome* is the patient-reported change in shoulder functional outcome between baseline and 6 months postoperatively as measured with the OSS.^38^ The OSS is a condition-specific questionnaire developed for patients with a degenerative or inflammatory state of the shoulder. It contains 12 items to be answered by the patient independently, which deal with pain (degree, time point) and possible handicaps in private and professional life. There are five categories of response to every question, corresponding to a score ranging from 0 to 4. Scores are summed to give a single score ranging from 0 (worst outcome) to 48 (best outcome). Transcultural validations of this questionnaire for the German and Italian populations have been performed^39 40^ and are validated for patient-based outcomes after rotator cuff repair.^41–43^ While functional outcome at the last 24-month follow-up is clinically relevant, the early 6-month primary time point is chosen because of the importance in early surgical recovery and rehabilitation, particularly when considering the socioeconomic impact on professionally active patients.^4^

The *second primary outcome* is the occurrence of shoulder stiffness within 6 months after surgery: this event is poorly defined in the literature.^19^ We formed a consensus definition of shoulder stiffness among specialised shoulder surgeons in a Delphi survey, which describes a postoperative restriction in passive shoulder motion diagnosed within 6 months after ARCR in at least two of the motion planes of flexion, abduction and external rotation in 0° abduction. Motion restriction is to be assessed separately for each plane according to specific threshold criteria (flexion: total motion equal to or below 90° or glenohumeral motion equal to or below 80°; abduction: total motion equal to or below 80° or glenohumeral motion equal to or below 60°; external rotation in 0° abduction: glenohumeral motion equal to or below 20° or no more than 50% of the contralateral side value). In this project, we will identify cases of shoulder stiffness based on our consensus definition as well as clinical records and reports from clinicians and their patients.

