Operative details and postoperative management will also be investigated: type of ARCR procedure (use of anchors, suture techniques), augmentation techniques (eg, platelet concentrates, scaffolds and so on),^62^ additional concomitant treatment (acromioplasty, acromioclavicular joint resection, capsulotomy, biceps tenotomy or tenodesis, treatment of SLAP lesion), duration of operation, duration of hospital stay, and postoperative management (immobilisation position and duration, pain medication (eg, using non-steroidal anti-inflammatory drugs), timing of passive and active shoulder motion, and physiotherapy and muscle training).

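### The primary models draw on operative and postoperative variables without screening on timing, so a final model that retains them could not be applied at the decision for surgery, its stated use

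*Protocol article*

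**What the plan says.** Under Predictive model development, the Protocol article fixes the source of predictors for both primary outcomes (change in OSS to 6 months, and shoulder stiffness): "The prediction of the model(s) will be based on the baseline, operative and postoperative management variables".

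The section Baseline prognostic factors lists the candidates. Despite its heading, it includes items that arise in theatre or later: "duration of operation, duration of hospital stay, and postoperative management". Under postoperative management it names immobilisation, pain medication and "timing of passive and active shoulder motion, and physiotherapy and muscle training".

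The intended use appears in three places:

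- Abstract, Ethics and dissemination: "This project contributes to the development of personalised risk predictions for supporting the surgical decision process in ARCR".
- Scientific relevance and broader impact: the models should "hence offer personalised health information to support future patients and surgeons in the decision process for surgery".
- Introduction: "Appropriate indication of ARCR and judgement on risks of AEs or unsatisfactory patient outcomes rely on validated clinical prediction tools".

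The second primary outcome is defined under Outcomes as "a postoperative restriction in passive shoulder motion diagnosed within 6 months after ARCR".

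Predictors are narrowed first by Delphi ratings of prognostic value. Selection then uses AIC or adjusted R2 for continuous outcomes and the area under the ROC curve for stiffness. Performance is checked by calibration and discrimination, with bootstrapping for internal validation and application to validation data sets.

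**The concern.** A prediction model can be used only at a moment when all its inputs are known. The stated use places that moment before the operation, yet the stated predictor set extends past it. If terms such as hospital stay or the course of physiotherapy survive selection, a surgeon counselling a patient has no value to enter. The published discrimination and calibration would then describe a setting other than the one the model is meant for.

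For stiffness there is a further risk. The event can be diagnosed at any point up to 6 months, and postoperative management accrues over those same months. If a patient becomes stiff and physiotherapy or pain medication changes as a result, the recorded management partly reflects the outcome. Selection on AUC would favour such a variable.

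Any late-known terms that are retained also compete with preoperative ones for few places. Sample size determination plans at most 10 predictors for stiffness. With 920 patients, the expected events are 920 × 0.083 ≈ 76 at the pilot rate and 920 × 0.10 = 92 at the assumed rate.

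**Working it through.** The plan states no figure on this point, so there is none to reproduce. The check has three steps.

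**1. When each predictor group becomes known (from Baseline prognostic factors)**

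- *Patient, disease, imaging and baseline score variables:* before surgery, so available at the decision.
- *Intraoperative findings, procedures and operating time:* during surgery. A planned technique may be foreseeable; operating time is not.
- *Hospital stay:* after surgery.
- *Immobilisation, pain medication, timing of motion, physiotherapy and muscle training:* over the weeks and months after surgery. A prescribed scheme may be foreseeable; the actual course is not. This group overlaps the 6-month stiffness window.

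**2. Whether any planned step screens on timing (from Predictive model development)**

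- Delphi rating scores known or potential prognostic value only.
- AIC, adjusted R2 and AUC reward association, whatever the timing.
- Bootstrapping resamples the same records. It corrects for overfitting, and a variable that follows the outcome does so in every resample.
- Validation data with predictors recorded in the same way would carry the same feature.

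None of these removes a predictor that is unknown at the decision or that follows the event.

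**3. Illustration of size for stiffness**

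Only the 10% event rate comes from the article (Sample size determination). The rest is assumed: 400,000 simulated patients, one normally distributed baseline score with log odds ratio 0.4 or 0.75 per SD, and one binary management variable present in 30% of non-stiff patients and in 45%, 60% or 80% of stiff patients. That variable depends on stiffness alone, so it carries no preoperative information by construction.

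| Baseline-only AUC | Variable present in stiff patients | AUC with variable | Apparent gain | AUC with variable held at its mean | Mean predicted risk if variable entered as absent |
|---|---|---|---|---|---|
| 0.608 | 45% | 0.638 | 0.030 | 0.608 | 8.1% |
| 0.608 | 60% | 0.700 | 0.092 | 0.608 | 6.0% |
| 0.608 | 80% | 0.792 | 0.184 | 0.608 | 3.1% |
| 0.699 | 45% | 0.713 | 0.014 | 0.699 | 8.1% |
| 0.699 | 60% | 0.752 | 0.053 | 0.699 | 6.2% |
| 0.699 | 80% | 0.826 | 0.127 | 0.699 | 3.2% |

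The last column can be checked by hand with Bayes' rule, ignoring the baseline score. At 60% against 30%, the risk given that the variable is absent is 0.10 × 0.40 / (0.10 × 0.40 + 0.90 × 0.70) = 0.040 / 0.670 = 6.0%. At 45% it is 0.055 / 0.685 = 8.0%, and at 80% it is 0.020 / 0.650 = 3.1%. The true rate is 10% throughout.

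With no dependence on stiffness (30% in both groups) the AUC does not change. The apparent gain therefore runs from nil, through about 0.01, up to about 0.18, depending entirely on a dependence that the article gives no means to estimate.

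**The case against.** The case on the other side is substantial.

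- **The variables are candidates, not fixed terms.** Delphi rating and criterion-based selection may drop every one of them. This stands, and it makes the point conditional on what is retained. But the article says prediction will be based on all three groups, and nothing in the selection concerns timing.
- **Management factors are included on purpose.** The Abstract lists them for investigation, and the Introduction says individual predictions need relevant patient and management factors. The primary objective does not limit the models to preoperative use. This also stands: studying these factors is legitimate, and a postoperative prognostic model would be too. But the only decision the article names for its predictions is the one about surgery. It mentions updated versions of the models without defining staged ones.
- **Some items may be foreseeable.** The Intervention section describes clinic-specific standards and a usual three-phase rehabilitation scheme. A reader might infer from the candidate list that nothing operative or postoperative can be known at the decision; that is too strong. Operating time, hospital stay and the actual rehabilitation course remain unknown.
- **Reverse causation is not documented.** A reader might infer that stiffness does leak into the predictors and that the accuracy will be inflated. No section says management is recorded after stiffness or changed because of it. The Figure 1 legend mentions recall on rehabilitation, without saying how it will be coded. Adverse events are dated (AE documentation and assessment process), so predictors might be ordered against the event. The argument is also made only for stiffness, not for OSS change.
- **The SAP may settle it.** Staging and measurement windows are often fixed there, and it is not shown. The objection here is to a rule that the article does state, set against the purpose it states. If the SAP differs, the two need to be reconciled.

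**Conclusion.** The point holds in conditional form. The stated predictor set conflicts with the stated use, and no planned step resolves the conflict. A final model for either primary outcome that retains predictors unknown before surgery could not be applied at the decision it is meant to support. This part rests on the text alone.

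The second part is a risk for the stiffness model only. Because the windows overlap, postoperative management could follow from stiffness; AUC-based selection would favour such a variable, and bootstrapping would not reveal it. Its size is unknown. The illustrated gain of about 0.01 to 0.18 in apparent AUC, and a mean predicted risk of about 3% to 8% against a true 10%, depend on assumed inputs and are not estimates for this cohort.

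A reader might conclude that the models as planned cannot serve their purpose at all. The documents do not support that: selection may yield a model of preoperative variables only, and no section rules out a separate preoperative version.

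**What to change.** For each primary outcome, state the prediction time and let it determine the predictors:

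1. **Decision-support model:** only variables known before surgery (patient, disease, imaging and baseline scores). This is the headline model and the one behind any tool for deciding on surgery.
2. **Intraoperative model:** adds findings and procedures from the operation, labelled as usable from the end of surgery.
3. **Postoperative model:** adds management variables, with a stated prediction time after surgery.

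Each model should admit only values fixed by its prediction time. For stiffness, those values must also precede its diagnosis. Add this timing criterion to the Delphi step, so that factors are rated within the model they could enter.

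The change is one of wording, plus one or two extra models per outcome on data already planned for collection. The downside is that the headline model will probably show lower apparent R2 and AUC.
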